### 5.1 Definitions of data sets

- Page 6 von 22

- (2) The participants who completed the study without any major protocol violations (see chapter 5.2) will be analyzed in the **per protocol (PP)** data set. A PP analysis includes only those participants who adhered to all important aspects of the study protocol and, thus, provides an estimate of the optimal efficacy of anodal tDCS in comparison to sham stimulation.
- (3) The **safety (SA)** data set includes all randomized subjects who started at least 1 double-blind stimulation session (stimulation visits V1 to V10 between Baseline (T2) and Post (T3), see Figure 1). It will be the main data set for the analysis of safety and tolerability of anodal tDCS stimulation. Patients will be analyzed according to the actually received treatment.

## 5.2 Protocol violations

In general, a major protocol violation is defined as a relevant non-compliance to the study protocol that leads to exclusion of participants from the PP data set (Bhatt, 2012).

In both studies, E-StimADHD **Study A** and **Study B**, relevant protocol violations are:

(1) Protocol violations that lead to **exclusion** of the participant from the **per protocol analysis** (sham vs. verum at T3/V11):

- V0 or V11 is missing
- missing two or more of the ten stimulation sessions
- on two or more of the ten stimulation sessions, the total duration of stimulation was below 18 minutes for any reason including malfunction or incorrect use of the device
- the placement of tDCS electrodes was incorrect on two or more of the ten stimulation sessions
- stimulation medication at V0 and/or during stimulation (V1-V10) and/or at V11
- occurrence of a neurological or psychiatric disorder included in the exclusion criteria after screening
- start of participation in a clinical trial or neurofeedback after screening

(2) Further important protocol violations are **delayed visits** (e.g., due to sickness):

- time period between V1 and V10 exceeds 3 weeks
- time period between V10 and V11 is longer than 8 days

Participants with one or more protocol violations are excluded from PP analyses. The motivation is to ensure that comparisons are made between those participants only who adhered in important aspects to the study protocol.

The primary analysis will be based on the ITT set including all randomized participants. A PP analysis will be performed as sensitivity analysis. Occurring differences between both sets will be documented in the result report.

Further protocol violations regard only a subset of data:

Protocol violations relevant to the **analysis of V12**:

- V12 is missing
- the participant has been excluded from the analysis of V11

- period shorter than 4 weeks between V10 and V12
- Participant took **stimulant medication** between V11 and V12

Protocol violations relevant to the **analysis of questionnaire data**:

- questionnaires are returned more than 7 days after the respective visit

## 6. Variables and study endpoints

### 6.1 Demographic and baseline characteristics

For the full ITT data set and separately for the two study arms (**Study A**: left dlPFC; **Study B**: rIFG), demographic and baseline characteristics will be summarized using descriptive summary statistics. Absolute and relative frequencies will be reported for categorical and dichotomous variables. For metric variables the mean value, standard deviation, median, the interquartile range, minimum, and maximum will be calculated. Results will be presented using tables (see Table 1 in Appendix 1) and boxplots where appropriate.

Information about patients with ADHD and their parent(s) will be recorded at Visit 1.0 (T1 – Screening). Demographic data of ADHD patients will include the variables *gender*, *age*, *ethnicity*, *height*, *weight*, *Body Mass Index (BMI)*, and *BMI percentiles* (based on KIGGS reference data) and other variables related to their sociodemographic background (see Table 1). In addition, inclusion and exclusion criteria will be saved and documented as dichotomous variables (1=fulfilled, 0=not fulfilled, see Table 2 in Appendix 2). Dichotomous variables of inclusion and exclusion criteria will be summarized in absolute and relative frequencies and will be visualized in a CONSORT-Flow diagram.

Furthermore, patients' characteristics before any stimulation session will be summarized with descriptive statistics. This will include the variables *handedness* (Edinburgh Handedness Inventory, child rating), *socioeconomic status of the parents* (e.g., net income of the household, school graduation level, and current professional situation of the parents), *pubertal status* (Pubertal Development Scale, child and parent rating), *expectations and concerns towards tDCS* (survey of child and parent), *severity of ADHD symptoms* (ADHD rating scale, child and parent rating), and *quality of life* (KIDSCREEN-27, child and parent rating).

### 6.2 Primary endpoints

To measure effect sizes of changes in neuropsychological performance, study safety, and tolerability of multi-channel anodal tDCS (anodal tDCS vs. sham stimulation) in children and adolescents with ADHD, primary endpoints of the EStimADHD study were adapted to the specific stimulated brain area (**Study A**: left dlPFC; **Study B**: rIFG) and are presented separately below.

#### Study A:

The **n-back working memory task** is a continuous performance task that is commonly used as an assessment in cognitive neuroscience to measure working memory capacity (Gazzaniga, Ivry, & Mangun, 2009). In the n-back working memory task, a series of pictures is presented, with 25% of the n-back trials being target trials, which means that the currently

presented stimulus is identical with the stimulus  $n$  trials earlier (Kirchner, 1958). ADHD patients will be instructed to decide by button press if the current stimulus is a target or not.

The  $n$ -back working memory task is used in **Study A** to assess patients' working memory capacity. Hence, the primary endpoint is the **overall accuracy** (i.e., sum of correct hits, correct rejections, correct rejections 1lure, and correct rejections 2lure in percent, variable *nback\_oa*) in the  **$n$ -back working memory task** (Gazzaniga, Ivry, & Mangun, 2009) which assesses patients' working memory. The  $n$ -back task will be used throughout **Study A** and effectiveness of anodal tDCS stimulation will be evaluated by analyzing patients' performance at Visit V11 (T3: Post; see Figure 1), adjusted for performance at Visit V0 (T2: Baseline).

### Study B:

In the **flanker task** (target task), stimuli consist of five arrows. The middle arrow is the target stimulus and participants should indicate via button press with the right or with the left hand if the target arrow points to the right or to the left. The outer arrows serve as distractors and can point in the same direction (congruent trial) or in the opposite direction (incongruent trial). The flanker task provides information on cognitive interference control.

The primary endpoint for Study B is the **overall accuracy** (i.e., correct hits for congruent and incongruent trials in percent, variable *flanker\_oa*) in the flanker task. Effectiveness of anodal tDCS stimulation will be evaluated by analyzing patients' performance at Visit V11 (T3: Post; see Figure 1), adjusted for performance at Visit V0 (T2: Baseline).

For both **study A** and **study B**, safety and tolerability of tDCS assessed by (1) a standardized safety questionnaire as well as (2) EEG recordings before and after tDCS (EEG abnormalities such as slowing under the stimulating electrode or in remote brain areas, polarization asymmetries, spike-and-wave discharges) and (3) number, type, and severity of adverse events (AEs, variables *ad*, *ad\_type*, and *ad\_sev*) and severe adverse events (SAEs, variables *sae*, *sae\_type*, and *sae\_sev*) are defined as primary endpoints.

***Note: Statistical analyses for raw EEG recordings are not included in this SAP. No raw EEG data will be analyzed by the IMIS. However, defined aggregated EEG data (defined abnormalities coded e.g., in SPSS files) as relevant for safety will be analyzed.***

As an overall safety analysis of all STIPED studies, the safety endpoints ((S)AEs and safety questionnaire) will also be analyzed for Study A and Study B together (and furthermore also together with the safety data of the other studies in WP3, WP4 and WP5, details of this analysis will be specified elsewhere) in order to get a global safety assessment of tDCS in children and adolescents.

### 6.3 Secondary endpoint(s)

In addition to the primary endpoints, specific measures of the neuropsychological tasks will be used as secondary endpoints, such as accuracy, commission and omission errors, reaction time, and reaction time variability as secondary endpoints. Each of these secondary endpoints will be measured before (V1) and after (V11/V12) verum or sham stimulation and

effectiveness will be assessed by comparing the values after stimulation between study arms (tDCS vs sham) adjusted for baseline values. In addition, the measures of the primary outcome (overall accuracy in n-back or flanker task) at the follow-up visit (V12) will be secondary endpoints.

For both **Study A** and **Study B**, severity of **ADHD symptoms** (inattention, hyperactivity/impulsivity) and **quality of life** (KIDSCREEN-27) as assessed by questionnaire at V11 and V12 will be secondary endpoints.

Secondary endpoints at V11 and V12 for **Study A** in the **target task** (n-back working memory task) are:

- The **reaction time** (variable *nback\_rt*) for the overall accuracy in the n-back working memory task.
- The **variability of the reaction time** for the overall accuracy (i.e., standard error, variable *nback\_rtSD*) in the n-back working memory task.
- All **omission errors** (i.e., sum of all missed target trials, variable *nback\_omiss*) in the n-back working memory task.
- All **commission errors** (i.e., sum of all false alarms, false alarms 1lure, and false alarms 2lure, variable *nback\_comiss*) in the n-back working memory task.

Secondary endpoints at V11 and V12 for **Study A** in the **first non-target task** (flanker task) are:

- The **overall accuracy** (i.e., sum of correct responses for congruent and incongruent trials in percent, variable *flanker\_oa*) in the flanker task.
- The **reaction time** (variable *flanker\_rt*) for the overall accuracy in the flanker task.
- The **variability of the reaction time** for the overall accuracy (i.e., standard error, variable *flanker\_rtSD*) in the flanker task.
- All **omission errors** (i.e., sum of all omission errors for congruent and incongruent trials, variable *flanker\_omiss*) in the flanker task.
- All **commission errors** (i.e., sum of all commission errors for congruent and incongruent trials, variable *flanker\_comiss*) in the flanker task.

The Continuous Performance Task (CPT) is the **second non-target task** in Study A. In the CPT, various upper case letters will be presented. One of the letters will be defined as a cue and one as a target stimulus. Whenever the cue is followed by the target stimulus, participants are instructed to press a button. However, participants should withhold their response if the cue is followed by another stimulus. Secondary endpoints at V11 and V12 for Study A in the CPT are:

- The **overall accuracy** (i.e., sum of correct neutral, correct cues, correct non-targets, and correct targets, variable *CPT\_oa*) in the CPT.
- The **reaction time** (variable *CPT\_rt*) for the overall accuracy in the CPT.
- The **variability of the reaction time** for the overall accuracy (i.e., standard error, variable *CPT\_rtSD*) in the CPT.
- All **omission errors** (i.e., sum of all missed targets, variable *CPT\_omiss*) in the CPT.
- All **commission errors** (i.e., sum of all false alarms, false alarms for cues, and false alarms for non-targets, variable *CPT\_comiss*) in the CPT.

Secondary endpoints at V11 and V12 for **Study B** in the **target task** (flanker task) are:

- The **reaction time** (variable *flanker\_rt*) for the overall accuracy in the flanker task.
- The **variability of the reaction time** for the overall accuracy (i.e., standard error, variable *flanker\_rtSD*) in the flanker task.
- All **omission errors** (i.e., sum of all omission errors for congruent and incongruent trials, variable *flanker\_omiss*) in the flanker task.
- All **commission errors** (i.e., sum of all commission errors for congruent and incongruent trials, variable *flanker\_comiss*) in the flanker task.

Secondary endpoints at V11 and V12 for **Study B** in the **first non-target task** (n-back working memory task) are:

- The **overall accuracy** (i.e., sum of correct hits, correct rejections, correct rejections 1lure, and correct rejections 2lure in percent, variable *nback\_oa*) in the n-back working memory task.
- The **reaction time** (variable *nback\_rt*) for the overall accuracy in the n-back working memory task.
- The **variability of the reaction time** for the overall accuracy (i.e., standard error, variable *nback\_rtSD*) in the n-back working memory task.
- All **omission errors** (i.e., sum of all missed target trials, variable *nback\_omiss*) in the n-back working memory task.
- All **commission errors** (i.e., sum of all false alarms, false alarms 1lure, and false alarms 2lure, variable *nback\_comiss*) in the n-back working memory task.

Secondary endpoints at V11 and V12 for **Study B** in the **second non-target task** (CPT) are:

- The **overall accuracy** (i.e., sum of correct neutral, correct cues, correct non-targets, and correct targets, variable *CPT\_oa*) in the CPT.
- The **reaction time** (variable *CPT\_rt*) for the overall accuracy in the CPT.
- The **variability of the reaction time** for the overall accuracy (i.e., standard error, variable *CPT\_rtSD*) in the CPT.
- All **omission errors** (i.e., sum of all missed targets, variable *CPT\_omiss*) in the CPT.
- All **commission errors** (i.e., sum of all false alarms, false alarms for cues, and false alarms for non-targets, variable *CPT\_comiss*) in the CPT.

In addition to secondary endpoints resulting from target and non-target tasks, **readout measures** common for **both Study A and B** will be assessed as additional secondary endpoints.

- Functional brain related outcome measures based on EEG: (1) functional and effective connectivity in the resting state EEG; (2) event related potentials: amplitude, latency variability, neuronal sources of task relevant components, power changes before and after stimuli in the single-trial analysis.

- Structural and functional and structural brain related outcome measures based on MRI: (1) gray and white matter thickness based on voxel based morphometry, cortical thickness and folding, gyrification index; (2) structural connectivity based on parameters of functional anisotropy and fiber tractography (DTI measures); (3) resting state functional connectivity as well as Graph theoretical measures (connectivity density; local and global efficacy e.c.) based on BOLD fMRI.

***Note: The IMIS is not responsible for the above mentioned readout measures. Statistical analyses for these readout measures are not included in this SAP. No raw EEG or MRI data will be analyzed by the IMIS. However, aggregated EEG/MRI data (e.g., in SPSS files) may be analyzed in some cases.***

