| Resting state fMRI                                                                   |                 |                                | x*     |                         |    |                                                                            |    |    |    |    |    |    |     |                          | x*      |                           |
| DTI                                                                                  |                 |                                | x*     |                         |    |                                                                            |    |    |    |    |    |    |     |                          |         |                           |
| Assessment of arousal/motivation                                                     |                 | x                              | x*     | x                       | x  | x                                                                          | x  | x  | x  | x  | x  | x  | x   | x                        | x*      | x                         |
| 64-channel EEG (resting state)                                                       |                 | x                              |        |                         |    |                                                                            |    |    |    |    |    |    |     | x                        |         | x                         |
| 64-channel EEG (n-back / Flanker / CPT)                                              |                 | x                              |        |                         |    |                                                                            |    |    |    |    |    |    |     | x                        |         | x                         |
| Stimulation (real/sham) + task (Study A: n-back; Study B: Flanker)                   |                 |                                |        | x                       | x  | x                                                                          | x  | x  | x  | x  | x  | x  | x   |                          |         |                           |

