#### 2.2.2 Secondary endpoints

- Severity of ADHD symptoms (inattention, hyperactivity/impulsivity): changes from screening/ V0 to V11 and V12
- **Study A:** Reaction time and reaction time variability in n-back task, number of omission and commission errors: changes from V0 to V11 and V12  
**Study B:** Reaction time and reaction time variability in Flanker task, number of omission and commission errors in congruent and incongruent trials: changes from V0 to V11 and V12
- Performance measures in neuropsychological tasks that assess impaired functions in ADHD but are different from the task presented during stimulation accuracy and reaction times / reaction time variability in  
**Study A:** (1) Flanker task and (2) and a Continuous Performance task (CPT): changes from V0 to V11 and V12  
**Study B:** (1) n-back working memory task and (2) and a Continuous Performance task (CPT): changes from V0 to V11 and V12
- Functional brain related outcome measures (1) *resting state EEG*: connectivity, phase coherence, Granger causality (2) *event related potentials*: amplitude, latency, latency variability, neuronal sources of task relevant components: changes from V0 to V11 and V12 (3) *resting state fMRI*: changes from V0 to V11
- Quality of life: changes from Screening/V0 to V12

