**Visit 1 to 10 (V1 within 4 weeks after V0)**

- Assessment of arousal, mood and motivation before and after the session (SAM, VAS, diary)
- Multichannel stimulation (sham/real) of either the dlPFC (**Study A**) or the rIFG (**Study B**) during a task
- EEG before and after the multichannel stimulation
- Assessment of adverse events during stimulation (safety questionnaire)
- Assessment of adverse events

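### SAP 6.3 defines three secondary-endpoint details in conflict with the protocol or with itself: baseline visit (V1), quality of life at V11, and reaction-time variability as a standard error

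*Combined protocol and SAP*

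**What the plan says.** **Baseline visit.** SAP 6.3 sets the timing of the task-based secondary endpoints: "Each of these secondary endpoints will be measured before (V1) and after (V11/V12) verum or sham stimulation". It then says the arms are compared after stimulation with adjustment for baseline. Elsewhere V1 is a treatment visit. SAP 5.1 refers to "stimulation visits V1 to V10 between Baseline (T2) and Post (T3), see Figure 1", and Protocol 7.2 heads the block "Visit 1 to 10 (V1 within 4 weeks after V0" and lists randomisation under V0. In the protocol's Examination plan, the row marked for V1 to V10 is "Stimulation (real/sham) + task (Study A: n-back; Study B: Flanker"; the full set of three tasks is marked only at V0, V11 and V12. Protocol 2.2.2 defines the task endpoints as changes from V0.

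**Quality of life.** SAP 6.3 says that ADHD symptoms and KIDSCREEN-27 "as assessed by questionnaire at V11 and V12 will be secondary endpoints". Protocol 2.2.2 has "Quality of life: changes from Screening/V0 to V12".

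**Reaction-time variability.** SAP 6.3 defines it "for the overall accuracy (i.e., standard error, variable", followed by a variable name ending in rtSD. This occurs six times: three tasks in each of two studies. The protocol gives no formula.

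**Structural imaging (minor).** SAP 6.3 also lists, among further secondary endpoints, "structural connectivity based on parameters of functional anisotropy and fiber tractography (DTI measures", together with grey- and white-matter measures.

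**The concern.** A baseline covariate should be measured before treatment starts. A V1 value is taken after randomisation and during real or sham current. If stimulation acts at once, that value already carries part of the effect, and adjusting for it removes that part from the V11 comparison.

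A listed endpoint with no scheduled data collection will appear as planned and then be missing.

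A standard error is not a measure of a child's variability. It is that variability divided by the square root of the number of trials used. If that number rises with accuracy, the measure takes in some of the primary outcome, and an accuracy gain would look like steadier responding.

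These are the definitions an analyst would program from. Leaving them open to two readings allows the choice to be made after the data are seen.

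**Working it through.** The only power figure in the documents is Protocol 11.1: d = 0.6, two-sided alpha 0.05, power 80%, 45 per group. An exact two-sample t-test gives 44.59, so 45; 45/0.9 = 50 per arm. It reproduces, and nothing below depends on it.

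**1. Which measures have a V1 value?** Per study, SAP 6.3 lists 4 target-task measures plus 5 for each of two non-target tasks: 4 + 5 + 5 = 14. Only the target task is run at V1, so 5 + 5 = 10 have no V1 value. The other 4 do, because Protocol 7.3 records task performance at every intervention session.

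**2. Is a V1 value comparable with V11?** Protocol 7.3 gives 184 Flanker trials per block, four blocks at V1–V10 and two at V0, V11 and V12.
- V1: 4 × 184 = 736 trials.
- V0, V11, V12: 2 × 184 = 368 trials.

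The error endpoints are sums, so at equal error rates the V1 count is twice the V11 count. As a regression covariate, a constant factor of 2 is absorbed by the slope; in a change score, the form used in Protocol 2.2.2, it is not. Protocol 8.1 adds that stimuli are identical at T2, T3 and T4 but vary over the intervention sessions.

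**3. What would adjusting for V1 do?** Let D11 and D1 be the arm differences at V11 and V1, and b the slope of V11 on V1. The adjusted effect is D11 − b × D1, so the share removed is b × (D1/D11). The documents give neither b nor D1/D11. The direction follows if the V1 effect has the same sign as the V11 effect and b is positive; the size cannot be derived.

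**4. Quality of life by visit.**

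| Source | Screening | V11 | V12 |
|---|---|---|---|
| SAP 6.3 | not stated | yes | yes |
| Protocol 2.2.2 | yes (Screening/V0) | no | yes |
| Examination plan | yes | no | yes |
| Protocol 7.2 | yes | no | yes |

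The overview of protocol changes up to version 1.3 adds no V11 collection. ADHD symptoms, in the same SAP sentence, are collected at V11 and V12.

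**5. Standard error against standard deviation.** SE = SD/√m, with m the number of reaction times used.
- Flanker at V11, all 368 trials used: SD/SE = √368 = 19.2.
- n-back: √300 = 17.3 at 100 trials per run, or √375 = 19.4 if each 5-minute run is filled with 2.4-second trials.

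If m were the same for everyone, SE would only rescale SD and the p-value would not change. The difficulty comes when m varies. If only correct responses count, m is proportional to accuracy, and at constant SD the SE changes by √(a1/a2) − 1. All accuracy levels here are assumed:
- 75% to 80%: √(0.75/0.80) = 0.968, a fall of 3.2%.
- 75% to 85%: √(0.75/0.85) = 0.939, a fall of 6.1%.
- 70% to 90%: √(0.70/0.90) = 0.882, a fall of 11.8%.

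**The case against.** The strongest reply is that V1 is a typing slip. SAP 6.2 and 7.3 put the primary baseline at V0 (T2), Appendix 4 uses the _T2 variable, SAP 7.4 reuses that model with the outcome's own baseline, and the SAP says it is based on the protocol. The literal reading cannot be carried out for 10 of 14 measures. This stands as the likely explanation, so a reader who inferred that the plan deliberately adjusts for an on-treatment value would go too far. It does not remove the need for correction, because 7.4 names no visit and target-task data exist at V1. The SAP's use of Visit 1.0 for screening does not rescue the sentence, since no task is run at screening.

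A reader might also put a figure on the loss. A slope of 0.5–0.7 and a V1 effect of 25–50% of the V11 effect give 0.5 × 0.25 = 12.5% to 0.7 × 0.5 = 35%. Both inputs are assumptions with no source in the documents, so this range is not a finding.

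On variability, the name rtSD suggests that a standard deviation may be what is computed. The link to accuracy is conditional, because the documents do not say which trials enter the reaction time. For CPT it does not follow as stated: only the cue–target sequence calls for a press, whereas overall accuracy also counts correctly withheld responses, which yield no reaction time. A general claim that the measure is contaminated by accuracy is not supported.

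On structural MRI and DTI, the SAP's own note places the analysis of these readouts outside this plan, and Protocol 2.3 already uses baseline MRI to predict response. What remains is a listing problem: they are acquired only at V0_MRI.

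**Conclusion.** Three definitions in SAP 6.3 are wrong as written and should be corrected.

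- **Baseline at V1:** conflicts with Protocol 2.2.2 and with the SAP's own visit scheme. It leaves 10 of 14 task measures per study without a baseline. For the other 4 it would, if followed, adjust for an on-treatment value and could remove part of any effect, by an amount the documents do not allow one to state.
- **Quality of life at V11:** no collection is scheduled, so the endpoint has no planned data. This biases no estimate and leaves V12 untouched.
- **Variability as a standard error:** conflicts with the variable name in all six entries and makes the value depend on trial count. The 3–6% fall applies to n-back and Flanker only, and assumes that correct responses alone are used, that the spread is constant, and that accuracy rises from 75% to 80–85%.

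Only secondary endpoints are affected. This is an internal inconsistency of minor to moderate severity. It does not support any conclusion that the primary analysis, alpha, power or sample size is at fault.

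**What to change.** In SAP 6.3:

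1. Replace V1 by V0 (T2) as the baseline for all task-based secondary endpoints, and name that visit in 7.4 as well.
2. List quality of life at V12 only, with screening as its baseline. Keep ADHD symptoms at V11 and V12.
3. In all six entries, define reaction-time variability as the within-person standard deviation of reaction times, and state which responses enter it.
4. As a minor tidy-up, do not list structural MRI and DTI as post-treatment outcomes; describe them as baseline measures analysed outside this SAP.

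The cost is SAP wording only. No data collection, visit or sample-size change is needed. The correction should be dated before any unblinded analysis.

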#### N-back task

We will use the **n-back task** (Figure 4, right lower panel) with  $n=2$ . For this purpose, a series of objects will be presented with 25% of the trials being target trials meaning that the current stimulus is identical with the stimulus two trials earlier. Thus, the task requires continuous processes of encoding, retrieving and updating contents of working memory. The presented objects in each block consist of 10 different photographs that are presented 10 times each and serve as a target twice. Each trial has a duration of 2400 ms of which each object is displayed for 500 ms, preceded by a fixation cross for 1900 ms. The task will be conducted for 3 runs (5 minutes per run) with 1 min. pauses in between.

[figure not shown]

Figure 4. Examples of single trials of the Flanker task, the Continuous Performance task (V0, V11, V12) and the n-back working memory task

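### SAP 6.3 defines reaction-time variability as a standard error, so the score mixes a child's spread with the number of trials that carry a reaction time

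*Combined protocol and SAP*

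**What the plan says.** Protocol 2.2.2 lists, for Study A, "Reaction time and reaction time variability in n-back task, number of omission and commission errors" and, for Study B, "Reaction time and reaction time variability in Flanker task". It also lists reaction-time variability in the tasks not used during stimulation. It gives no formula.

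SAP 6.3 supplies one. For the n-back, the Flanker and the CPT, in both studies, it describes variability of the reaction time "for the overall accuracy (i.e., standard error, variable", and then names `nback_rtSD`, `flanker_rtSD` or `CPT_rtSD`. That makes six bullets, each with *standard error* in the text and SD in the variable name. No divisor, set of trials or minimum trial count is stated.

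SAP 6.2 defines n-back overall accuracy as the "sum of correct hits, correct rejections, correct rejections 1lure, and correct rejections 2lure in percent". SAP 7.4 analyses every secondary endpoint with the primary regression model, adjusted for the baseline value of that endpoint.

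**The concern.** Reaction-time variability means how widely one child's responses scatter. A child's standard error answers a different question: how precisely that child's mean is known. It shrinks as more trials enter, even if the scatter is the same.

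SAP 6.3 ties reaction time to overall accuracy, which implies that correct trials are used, although it does not say so outright. On that reading the number of usable trials in the n-back and Flanker tasks rises with accuracy. If stimulation improved accuracy and left the scatter alone, the variability score would still shift in favour of stimulation. A report of better accuracy together with lower variability could then be partly one effect shown twice. This matters for interpretation because Protocol 1.1 cites reduced reaction-time variability, beside better interference control, as prior evidence for rIFG stimulation.

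The conflict between gloss and name is a problem in its own right: two analysts could follow the same SAP and compute different endpoints.

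**Working it through.** **Plan's own figure.** The plan gives no figure for this endpoint. The arm size used below comes from Protocol 11.1 and reproduces: a two-sided t-test with d = 0.6, alpha 0.05 and 80% power needs 44.6, so 45 per group; 45 / 0.90 = 50 with 10% drop-out.

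**Trials presented at V0, V11 and V12 (Protocol 7.3).**
- n-back: "10 different photographs that are presented 10 times each" gives 100 per block, times 3 runs = 300. Run length gives 3 × 300 s / 2.4 s = 375 instead; the choice does not affect the percentages below.
- Flanker: 184 × 2 blocks = 368.
- CPT: 20 target sequences × 3 runs = 60.

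SAP 6.2 says of the n-back that "ADHD patients will be instructed to decide by button press if the current stimulus is a target or not", so correct rejections can carry a reaction time. I assume that they do.

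**Formula.** SE = SD / √n, with n = N × accuracy for the n-back and Flanker. At unchanged SD, moving from accuracy a0 to a1 multiplies the SE by √(a0/a1), and N cancels. A rise in true SD of √(a1/a0) − 1 cancels the fall exactly.

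| Accuracy | Change in SE at equal SD | Rise in SD that cancels it |
|---|---|---|
| 60% to 70% | −7.4% | 8.0% |
| 70% to 80% | −6.5% | 6.9% |
| 80% to 85% | −3.0% | 3.1% |
| 80% to 90% | −5.7% | 6.1% |
| 90% to 95% | −2.7% | 2.7% |

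Example with an assumed SD of 200 ms and 300 n-back trials: 200/√210 = 13.80 ms at 70% accuracy and 200/√240 = 12.91 ms at 80%. The within-child SD itself would not change.

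**Between arms.** The documents give no accuracy level, accuracy SD or between-child spread of variability, so these are assumptions: 45 per arm, 300 trials, mean accuracy 80% (sham) against 86% (stimulation) with SD 10 points, the same true distribution of reaction-time SD in both arms, and an unadjusted t-test. The SE ratio at these means is √(0.80/0.86) = 0.964, a fall of 3.6%. Simulation gives:

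| Between-child SD of log(reaction-time SD) | Spurious d on SE | Rejections, SE endpoint |
|---|---|---|
| 0.15 | −0.21 to −0.22 | 16.5% to 17.5% |
| 0.25 | −0.14 | 9.5% to 10.5% |
| 0.35 | −0.09 | 7.7% |

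Ranges are from repeated runs. The same test on the SD rejects in about 5%.

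A wider grid (accuracy benefit of d = 0.6, sham accuracy 70 to 90%, accuracy SD 5 to 10 points) gives a spurious d of 0.05 to 0.25 and 5.5 to 22% rejections unadjusted. If baseline adjustment achieves a correlation of 0.7, the range is 6 to 38%.

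**CPT.** Only target hits carry a reaction time. Going from 45 to 51 hits changes the SE by √(45/51) − 1 = −6.1%. Accuracy gained by correctly withholding responses adds no reaction time and changes n by nothing.

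**Unfinished tasks.** Completing 2 of 3 n-back runs multiplies the SE by √(3/2) = 1.22; completing 1 of 2 Flanker blocks multiplies it by √2 = 1.41.

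**Reach.** Three variables × two visits × two studies = 12 planned analyses. Eight concern the n-back or Flanker and four the CPT. In only four (n-back in Study A, Flanker in Study B, at V11 and V12) is the task the one whose accuracy is primary.

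**The case against.** The strongest reply is that *standard error* is a slip. All six variable names say SD, the protocol asks for variability, and the programmer may well compute an SD. That is quite possible, and it means that the harm is conditional on the text being followed. It does not remove the contradiction: the explicit gloss appears six times and no other passage corrects it.

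A reader might infer that the score falls whenever accuracy improves. The documents do not support that. A modest rise in true SD cancels the effect, as the first table shows. If a child's log-SD varies by 0.05 to 0.20 between visits (assumed), the SE fails to fall in 9 to 37% of children who go from 70% to 80% accuracy, and in 27 to 44% of those who go from 80% to 85%.

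A reader might also infer that all 12 analyses are contaminated by the primary endpoint. They are not. CPT overall accuracy counts withheld responses that have no reaction time, and in eight analyses the task is not the stimulated one, so there is less reason to assume a gain of six points.

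The figures for unfinished runs need a limit too. The design fixes the number of trials presented at each assessment visit, and nothing suggests that incompletion would differ by arm. Without such a difference they mean added noise, not bias.

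Finally, the simulated rates omit the baseline adjustment in SAP 7.4, so they are not those of the planned model. As the wider grid shows, adjustment could raise them.

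**Conclusion.** The definition is wrong as written and contradicts its own variable names. Followed literally, it replaces a measure of spread with one that also depends on the number of usable trials.

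The arithmetic link to n is certain. The link to accuracy in the n-back and Flanker rests on correct trials being used, as SAP 6.3 implies. The size is modest: about 3 to 7% of the score for accuracy gains of 5 to 10 points at unchanged spread. The between-arm results, a spurious d of about 0.1 to 0.2 and roughly 8 to 17% rejections, rest entirely on assumed inputs and presuppose a real accuracy benefit. The link to overall accuracy is weaker in the CPT.

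Only secondary endpoints are touched. SAP 7.3 concludes superiority from the primary-endpoint coefficient alone; that endpoint, its model and the sample size are unaffected. This should be fixed, but it does not threaten the main conclusion.

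**What to change.** In all six variability bullets of SAP 6.3, replace *standard error* with the within-child standard deviation of single-trial reaction times on correct responses; for the CPT, on correct target hits. Stating a minimum number of usable trials at the same place would be helpful.

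The cost is a wording change in six bullets, made before unblinding. The variable names already fit. No new data are needed, because Protocol 8.1 describes log files that record every stimulus and response.
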